## Abstract

**Background:**

Early withdrawal or exclusion from the labor market leads to significant personal and societal costs. In Norway, the increasing numbers of young adults receiving disability pension is a growing problem. While a large body of research demonstrates positive effects of Supported Employment (SE) in patients with severe mental illness, no studies have yet investigated the effectiveness of SE in young adults with a range of social and health conditions who are receiving benefits.

**Methods/design:**

The SEED-trial is a randomized controlled trial (RCT) comparing traditional vocational rehabilitation (TVR) to SE in 124 unemployed individuals between the ages of 18-29 who are receiving benefits due to various social- or health-related problems. The primary outcome is labor market participation during the first year after enrollment. Secondary outcomes include physical and mental health, health behaviors, and well-being, collected at baseline, 6, and 12 months. A cost-benefit analysis will also be conducted.

**Discussion:**

The SEED-trial is the first RCT to compare SE to TVR in this important and vulnerable group, at risk of being excluded from working life at an early age.

**Trial registration:**

Clinicaltrials.gov, registration number NCT02375074. Registered on December 3rd 2014

## Background

### Early disability

The number of young adults receiving permanent disability pension in Norway has recently accelerated. While the overall percentage of disability pensioners in the population has remained steady for the last decade, there has been an increase in the proportion of young disability pensioners (between 18 and 29 years old) and a continuous decline in older disability pensioners throughout the same period [1, 2]. From 2006 to 2015 there was an increase of 77 % in young disability pensioners [3] while the population in the same age group increased by 23 % [4], making the development evident even when population growth is accounted for. Additionally, during the same period, an increased rate of labor immigration (mainly young males) has inflated the number of working young adults, which may have suppressed the percentage growth and led to an underestimation of the development [1].

Musculoskeletal and common mental disorders account for about 2/3 of sickness benefits and disability pensions issued in Norway [5, 6], but within the subgroup of disability pensioners aged 18–29, 59 % are receiving disability pensions due to mental illness and behavior disorders alone [7]. This type of early withdrawal or exclusion from the labor market leads to vast personal and societal costs, especially when seen in context with the aging of the Norwegian population causing a disparity between the supply of available workforce and the need of work capacity [8]. Furthermore, the importance of work for health and well-being is well-documented [4–6], and evidence shows that unemployment is not only caused by mental health problems, but also causes them [7, 8].

Long-term sickness absence is a risk factor for unemployment and permanent disability that goes beyond the effect of health status, suggesting that long-lasting absence may itself initiate a process of marginalization from the labor market [9]. Few recipients of long-term sickness benefits return to working life, seemingly due to mechanisms other than age, diagnosis, gender and public health [10]. This may be particularly relevant for young people in need of special assistance to obtain work, who are at risk of being excluded from working life before having had the chance to establish themselves on the labor market. Previous studies document that a small percentage of the population accounts for the majority of sickness absence, and that broad interventions targeting the workforce as a whole may not reach these small but high-risk groups [11]. Focusing on the group of young people who are receiving temporary benefits, but have not reached the point of more permanent disability pensions, thus appears to be a viable way to move forward.

### Perspectives in vocational rehabilitation

Vocational rehabilitation has traditionally been characterized by a *train-then-place principle*, involving prevocational training in sheltered environments before attempting to enter the open labor market [12]. In the train-then-place approach, clients try different forms of work adapted to their skills and challenges, while undergoing a stepwise process of targeted training to prepare them for competitive employment. Training is usually provided in group settings along with other workers with challenges or disabilities, and with close follow-up from an advisor. While the goal is to improve clients’ opportunities for obtaining work, the approach has been criticized for promoting dependency and demoralization [13], and for having a negative effect on different stakeholders expectations of the clients’ work ability and productivity [14].

In the 1980s, rehabilitation leaders in the U.S. introduced an approach based on the *place-then-train principle*, with a main goal of competitive employment and immediate work integration, without prevocational training [12]. This approach challenged common assumptions about people with serious disabilities being able to work only in workshops or other sheltered environments. Approaches within this perspective are known as Supported Employment (SE), and the evidence-based and manualized methodology of SE is called Individual Placement and Support (IPS). The model was originally developed for people with severe mental illness (SMI), and is supported by evidence from randomized controlled trials (RCT’s) in the US [15–24] as well as internationally [25–37], showing SE to be effective in this disability group on a range of vocational outcome measures. IPS involves individual support from a trained job specialist, incorporating eight evidence-based principles: focus on competitive employment in ordinary paid positions; rapid job search, starting the job search on average within one month after program entry; attention to the client’s choices and preferences; integrating work with mental health treatment; personalized benefits counseling; systematic job development; individualized long-term job support; and eligibility based on the client’s choice [38]. The latter involves a zero exclusion criteria, which states that everyone who has an expressed desire to work should have access to IPS services regardless of factors such as previous employment history, history of violent behavior, personal presentation, or substance abuse, and that the service does not screen for work readiness [39].

Evidence-based knowledge of the effectiveness of the services being offered through public agencies is of vital importance in future planning of vocational rehabilitation of young adults. Although there is a large and growing body of research demonstrating the effectiveness of the IPS approach in other populations, no studies have yet examined the effectiveness of IPS specifically for young adults at risk of becoming permanent disability pensioners.

## Methods/Design

The study is conducted by Uni Research Health, in collaboration with the Norwegian Labor and Welfare Administration (NAV).

### Aims and objectives

The aim of the project Supported Employment and preventing Early Disability (SEED-trial) is to compare two interventions to increase labor market participation in young people at risk of early work disability: Traditional Vocational Rehabilitation (TVR) versus Supported Employment (SE).

### Background measures

Each participant will be asked to complete questionnaires including background information on demographics and employment history.

### Outcome measures

#### Primary outcome: competitive employment

The primary outcome of the SEED-trial is *competitive employment at any time during the 12 months after enrollment in the study*. Competitive employment is here defined as working in a job on the competitive labor market, at usual wages, with regular supervision.

Additionally, success in employment will be defined using a range of standardized indicators of employment outcomes used in IPS studies [40], including rate of job acquisition, amount and duration of work, total wages, and number of days from enrollment in the study to employment. Information about receipt of social security benefits (sickness and disability benefits, unemployment, work assessment allowance), income, financial assistance, and educational activity (started or completed education), will also be collected.

We will use three sources of information for competitive employment: Survey data for hours worked and success in employment; register data from the NAV for receipt of social security benefits and income; and register data from Statistics Norway (SSB) for financial assistance and educational activity.

#### Secondary outcomes: self-reported health and well-being

Questionnaires distributed to all participants will further measure a range of secondary and non-vocational outcomes related to health and well-being, including interventions and treatment received for the last 6 months, experiences with bullying and violence, sleep problems, and the following variables:*Alcohol and drug abuse* will be measured using the 3-item Alcohol Use Disorders Identification Test (AUDIT-C) [41] screening for problem drinking, and the 11-item Drug Use Disorders Identification Test (DUDIT) [42] screening for drug-related problems and drug dependence.*Coping* will be measured using the 7-item Theoretically Originated Measure of the Cognitive Activation Theory of Stress (TOMCATS) [43], consisting of 3 subscales: coping (1 item), helplessness (3 items), and hopelessness (3 items).*Disability* will be measured using the 12-item version of the WHO Disability Assessment Schedule 2.0 (WHODAS 2.0), measuring functioning in 6 domains of life: cognition (2 items), mobility (2 items), self-care (2 items), getting along (2 items), life activities (2 items), and participation (2 items) [44].*Fatigue* will be measured using the 11-item Chalder Fatigue Questionnaire (CFQ) consisting of 2 subscales: physical fatigue (7 items) and mental fatigue (4 items) [45].*Illness perceptions* will be measured using the 9-item Brief Illness Perception Questionnaire (B-IPQ) [46], measuring 9 dimensions of illness perceptions: consequences (1 item), timeline (1 item), personal control (1 item), treatment control (1 item), identity (1 item), coherence (1 item), emotional representation (1 item), and concern (1 item), in addition to an open-ended item concerning causal factors (1 item).*Mental health* will be measured using the 25-item Hopkins Symptom Checklist (HSCL-25) [47], consisting of 2 subscales: anxiety symptoms (10 items) and depression symptoms (15 items).*Social support* will be measured using a revised 11-item version of the Social Support Inventory [48, 49] using 2 subscales as suggested by Øyeflaten et al. [50]: directive social support (4 items) and nondirective social support (7 items).*Subjective health complaints* will be measured using the 29-item Subjective Health Complaints Inventory (SHC), consisting of 5 subscales: musculoskeletal pain (8 items), pseudoneurology (7 items), gastrointestinal problems (7 items), allergy (5 items), and flu (2 items) [51].*Quality of life* will be measured using the 5-item EuroQol questionnaire (EQ-5D) including a visual analogue scale (EQ-VAS) [52].

### Participants and randomization

#### Inclusion and exclusion

Eligible participants will consist of unemployed individuals aged < 30 years old, who are receiving temporary benefits due to various social- or health-related problems. Attending employment services overseen by the NAV is a requirement for recipients of these benefits, and we will invite all those who are intended for the specific traditional employment service called “traineeship in a sheltered business”. The only additional exclusion criteria are that participants must have an expressed desire to work and sufficient language skills to answer questionnaires in Norwegian.

#### Recruitment and randomization

Nine local NAV-offices throughout the Hordaland County are involved in the project. Caseworkers at each office will refer all eligible participants to general information meetings organized by researchers at Uni Research Health in collaboration with NAV. The meetings include detailed information about the project and invitation to participate in the study. Interested individuals will be asked to read and give informed consent, and researchers will record their personal information (name, contact details, and national identification number) and provide each participant with an ID-number on the spot. ID-numbers will be randomized at Uni Research Health after the meetings, using premade computer-generated lists with a 1:1 randomization ratio. Information about randomization outcome will be communicated by e-mail or telephone to the relevant caseworker at NAV, who contacts their client and the relevant vocational rehabilitation organization.

### Data collection and data management

Survey data will be collected at baseline, 6 and 12 months. Baseline questionnaires will be administered at the information meetings, and participants complete their information electronically on iPads with secure software (Qualtrics®), or in paper format if preferred. Follow-up questionnaires will be administered electronically to participants providing their e-mail address at baseline, or in paper format via regular mail.

Data collected using iPads will automatically be electronically transferred to and stored in a secure online database. Data collected in paper form will be entered manually by the data manager at Uni Research Health and sent to the same database, after which the original questionnaires will be stored in a locked filing cabinet.

Register data will be collected retrospectively for 3 years before baseline, and for a 5-year period after enrollment date. The information will be de-identified and merged with survey data, while the identifier is secured in a locked and fireproof safe.

### Study design

The SEED-trial is designed as a randomized controlled trial (RCT), and participants are randomly assigned to 1 of 2 interventions (Fig. 1).

**Fig. 1 Fig1:**
[figure not shown]
Study design

#### Interventions

Both interventions in this trial are offered by VR organizations overseen by the NAV, and are part of the various employment schemes offered to people on temporary benefits in Norway. Participants continue to receive temporary benefits while attending the services, which are normally offered for up to two or three years, depending on the specific intervention and individual needs.

##### Traditional Vocational Rehabilitation (TVR)

The first group will be referred to a TVR organization, where they will receive a traineeship in a sheltered business with follow-up from trained advisors and department supervisors.

This intervention is *service as usual* for the study participants, and is currently offered to clients who are considered by their caseworker to have need for special assistance to obtain work. The specific approach falls within the *train-then-place principle*, and participants receive preparatory work training in a sheltered environment before pursuing employment. The goal of the intervention is to improve the participant’s work skills and opportunities for entering the labor market, and includes follow-up geared towards finding a job. The traineeships are offered by various sheltered businesses in the area with a range of departments including canteens and catering, car repair, day-care services, upholstery and interior decoration, transport, laundry services, welding, and warehouse handling. The distribution of participants to the various departments will follow usual practice, and is conducted at NAV based on the individual caseworker’s description of the client’s interests and goals, as well as availability and waiting-lists.

##### Supported Employment (SE)

The second group will be referred to the vocational rehabilitation organization Fretex Vest-Norge, where they will receive SE by trained job specialists following the evidence-based principles of IPS SE.

The intervention is based on the *place-then-train principle*, aiming to help people with health problems or other challenges participate in the competitive labor market, without the use of prevocational training, stepwise and sheltered approaches, or make-work jobs. It aims to find a good job match for the individual followed by on-the-job support after employment, and is based on a belief that anyone who wants to work can hold a job in the normal labor market as long as it is the right job and work environment for that individual.

#### Adaptions to the IPS SE model

As the manualized intervention of IPS SE was originally developed for patients with SMI, job specialists will need to make some adjustments to the services offered based on the individual participant’s challenges. One necessary adjustment concerns the principle of integrating employment services with mental health treatment, as that will not be applicable for participants that do not suffer from mental illness. In cases where participants are receiving treatment for other health problems, job specialists will establish contact with their respective health practitioners instead.

The implementation will be led by an experienced IPS trainer, who will also be in charge of the fidelity reviews, using the IPS fidelity scale [53], which is a standardized and validated scale for measuring adherence to the IPS model [54]. Fidelity reviews will be conducted using document review, calendar review, observations, and interviews of the different stakeholders, in order to determine to what degree the SE intervention fulfills the criteria for IPS SE. These evaluations will be used for quality improvement of services throughout the study period, aiming to adhere to the manualized and evidence-based treatment in spite of the necessary adaptions.

#### Sample size calculation

Our estimates of sample size are based on international input-data from previous IPS-studies where a mean competitive employment rate of 61 % has been found for IPS and 23 % for controls [55]. If we use 61 and 23 % as possible employment rates, we will need 31 participants in each group in order to obtain a statistical significant difference (with a 5 % significance level and power of 90 %). In order to enable stratified analyses to investigate treatment effects for sub-groups (e.g. for gender), we aim at including a total of 124 participants. The inclusion period will last for up to 2 years and close when the targeted number of participants has been reached.

#### Statistical analyses

Assessment of treatment effects will be analyzed using standard statistical methods, including t-tests for continuous data and chi-square tests for categorical data. Logistic regression will be performed to study potential moderators of treatment effects. For repeated measures over time (e.g. for sick leave), the statistical analyses may be extended to generalized estimation equations (GEE), to account for correlated data. All analyses will follow the intention to treat principle.

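### For continuous secondary outcomes with a baseline score, the only definite method named is the t-test; a baseline-adjusted model would be more precise at almost no cost

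*Protocol article*

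**What the plan says.** Under Statistical analyses, the protocol article gives the between-group methods in one sentence: "Assessment of treatment effects will be analyzed using standard statistical methods, including t-tests for continuous data", with chi-square tests where the data are categorical. Two further methods follow. Regression is reserved for effect modification: "Logistic regression will be performed to study potential moderators of treatment effects". For repeated measures, with sick leave as the example, "the statistical analyses may be extended to generalized estimation equations (GEE), to account for correlated data". No baseline covariate, ANCOVA or change score is mentioned. The article does not say whether a t-test would be applied to follow-up values or to change from baseline.

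Baseline values will exist. Data collection and data management states: "Survey data will be collected at baseline, 6 and 12 months". The abstract says the same of the secondary outcomes: "Secondary outcomes include physical and mental health, health behaviors, and well-being, collected at baseline, 6, and 12 months". Baseline questionnaires are completed at the information meetings, and ID-numbers are randomised after those meetings (Recruitment and randomization). The baseline scores therefore precede allocation and are legitimate covariates.

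**The concern.** The first measurement of a symptom or functioning scale usually predicts the later ones. A t-test on the 12-month value leaves that predictable between-person variation in the error term. Participants enter with a wide mix of social and health problems, so the variation may be considerable.

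The sample size was derived for the binary employment outcome, and nothing in the article sets the precision for the health scales. At stake is the width of the confidence intervals on those scales, and so the chance of seeing a health effect of Supported Employment if there is one.

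**Working it through.** **The plan's own figure.** The only sample-size calculation is for the primary outcome: 61% against 23%, 5% significance, 90% power. With unpooled variance and a two-sided test (sidedness is not stated, so this is assumed):

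n = [p1(1−p1) + p2(1−p2)] × (1.960 + 1.282)² / (p1−p2)² = (0.2379 + 0.1771) × 10.507 / 0.1444 = 30.2, rounded up to 31 per group.

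This matches the stated 31. It does not involve any continuous outcome, and nothing below changes it.

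**Inputs for the scales.**
- From the article: 124 participants and 1:1 allocation, so 62 per arm; a baseline score and two follow-ups.
- Assumed, because the article gives none of these: correlation r between baseline and follow-up of 0.3, 0.5 or 0.7; a true difference of 0.5 SD; equal variances at baseline and follow-up; two-sided 5% test.

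**Variance of the estimated difference, relative to a t-test on follow-up values (= 1).**
- t-test on change scores: 2(1 − r)
- baseline-adjusted (ANCOVA): 1 − r²

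| r | Follow-up t-test | Change-score t-test | Adjusted | Saving, adjusted vs follow-up | CI width, adjusted vs follow-up |
|---|---|---|---|---|---|
| 0.3 | 1.00 | 1.40 | 0.91 | 9% | 0.95 |
| 0.5 | 1.00 | 1.00 | 0.75 | 25% | 0.87 |
| 0.7 | 1.00 | 0.60 | 0.51 | 49% | 0.71 |

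The difference between the last two formulas is 2(1 − r) − (1 − r²) = (1 − r)², which is never negative. A change-score t-test therefore never beats adjustment, and it is worse than the follow-up t-test when r is below 0.5.

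**Equivalent size.** 62 / (1 − r²) gives 68, 83 and 122 per arm at r = 0.3, 0.5 and 0.7. That is the number a follow-up t-test would need to match 62 per arm with adjustment.

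**Power (noncentral t).** The noncentrality is 0.5 × √(62/2) = 2.78 for the follow-up t-test. For the adjusted analysis it is divided by √(1 − r²), giving 2.92, 3.21 and 3.90.

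| Analysis, 0.5 SD, 62 per arm | r = 0.3 | r = 0.5 | r = 0.7 |
|---|---|---|---|
| Follow-up t-test | 79% | 79% | 79% |
| Change-score t-test | 65% | 79% | 95% |
| Baseline-adjusted | 83% | 89% | 97% |

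With an assumed 50 responders per arm, the follow-up t-test has 70% power and the adjusted analysis 74%, 82% and 93%.

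**The case against.** Several points on the other side are sound.

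- **The list is open.** The methods are introduced as examples, so the article does not bind itself to an unadjusted test, and a change-score t-test is not ruled out. This stands, and it limits the point to what is named. Neither form of t-test beats adjustment.
- **GEE is available.** Scales taken three times fit the repeated-measures wording, and sick leave is only an example. But the analysis "may be extended to generalized estimation equations (GEE), to account for correlated data": it is optional, its stated purpose is correlation between measurements, and baseline is not named as a covariate. This softens the point without removing it.
- **Model detail belongs in the analysis plan.** Covariate lists often do, and a plan not shown here may already specify adjustment. However, the article names a method for continuous data, and a better one is available from data it already plans to collect. The point is a replacement for that method and does not rest on detail being absent.
- **The t-test is valid.** With complete data it is unbiased over randomisation, keeps its type I error, and already carries chance imbalance in its standard error. This stands in full.
- **Continuous data also covers vocational measures** such as wages and days to employment. Participants are unemployed at entry, so these have no informative baseline on the same measure. They are outside this point.

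A reader might also infer that GEE would fail here because it needs data missing completely at random. The article does not support so flat a statement: it gives no attrition figure, and with baseline covariates in the model missingness may depend on those covariates.

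**Conclusion.** The point holds as one of efficiency, on continuous secondary outcomes that have a baseline score. The t-test is the only definite between-group method named for them, and a baseline-adjusted analysis is more precise for any non-zero r than a follow-up t-test, and for any r below 1 than a change-score t-test. The variance saving against a follow-up t-test is modest at r = 0.3 (9%) and substantial from about r = 0.5 (25%, and 49% at r = 0.7). These figures rest on assumed correlations, and the power figures also on an assumed 0.5 SD difference.

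A reader might infer that the plan throws the baseline away and with it a large part of the precision. The article does not support this: it does not say which values the t-test uses, its list of methods is open, and it gives no correlation, effect size or response rate from which a loss could be stated as fact. Nor does it support any inference of bias, of an inflated type I error, or of an effect on the primary outcome or the sample size.

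**What to change.** In Statistical analyses, replace the t-test for scales measured at baseline, 6 and 12 months with one of two models:

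- ANCOVA at each follow-up, with arm and baseline score; or
- a linear mixed model on the 6- and 12-month values, with baseline score, arm, time and arm-by-time.

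Report the adjusted mean difference at 12 months with its 95% CI. The mixed model has a further advantage: it keeps participants who return only one follow-up questionnaire and is valid under missing at random, whereas a 12-month t-test drops anyone without that questionnaire. If GEE is preferred, state that the baseline score enters as a covariate.

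The cost is a change of analysis wording. No further data, participants or visits are needed, since the baseline questionnaire is already part of the planned collection.

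### Days from enrollment to employment is censored for anyone without a job, yet the only test named for continuous outcomes is the t-test and no named method handles censoring

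*Protocol article*

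**What the plan says.** In the protocol article, the section on the primary outcome defines that outcome as a yes/no measure: any competitive employment within 12 months of enrollment. It then adds further indicators of employment success, among them the "number of days from enrollment in the study to employment".

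The Statistical analyses section assigns methods by type of data. It promises standard methods, "including t-tests for continuous data and chi-square tests for categorical data". Logistic regression is reserved for moderators. For repeated measures, "the statistical analyses may be extended to generalized estimation equations (GEE), to account for correlated data". The section closes with: "All analyses will follow the intention to treat principle".

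No time-to-event method is named. Nothing says what value, if any, a participant who never starts a job receives for days to employment.

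The Sample size calculation section gives the planning rates: "a mean competitive employment rate of 61 % has been found for IPS and 23 % for controls". The target is 124 participants, randomised 1:1.

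**The concern.** A count of days is continuous, so the article's rule by data type leads to the t-test. But days to employment is known only for people who start a job. For everyone else the analyst knows only that the time exceeds their follow-up. The register follow-up of five years is longer than the survey follow-up but also finite, so it would reduce the censoring without removing it.

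If the t-test is run on the values that exist, it compares SE job finders with TVR job finders. Those two groups are selected after randomisation by the event that SE is meant to bring about, and at the planning rates they are selected in very different proportions. The comparison is no longer one of randomised groups. It ignores the main way in which SE could shorten time without work, which is that more people find a job at all. It can also count against SE any later placement of people who would otherwise not have worked.

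At stake is the trial's conclusion on speed of entry into work. That matters because the article names rapid job search among the principles of the intervention.

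**Working it through.** **Inputs from the article.** Rates 61% (IPS) and 23% (controls); 124 participants at 1:1, so 62 per arm; 12-month window for the primary outcome.

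**Assumptions.** The article gives no follow-up length for the 61% and 23%; they are read here as 12-month rates. It gives no timing of job starts, so several patterns are tried.

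**1. The plan's own figure.** The article says "we will need 31 participants in each group", "with a 5 % significance level and power of 90" per cent. With a two-sided test (assumed) and the unpooled normal approximation:

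n = (1.960 + 1.282)² × (0.61×0.39 + 0.23×0.77) / 0.38² = 30.2, rounded up to 31.

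The figure reproduces. It rests on the binary outcome, and the present point does not touch it.

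**2. Who has a value for days to employment.**
- SE: 62 × 0.61 = 37.8, about 38.
- TVR: 62 × 0.23 = 14.3, about 14.
- No value: 124 − 52 = 72, or 58% of those randomised (39% of SE, 77% of TVR).

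**3. Constant hazard in each arm.** λ = −ln(1 − p)/365, so 1/λ is 387.6 days for SE and 1,396.5 days for TVR (hazard ratio about 3.6).

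Mean days among finders = 1/λ − 365(1 − p)/p:
- SE: 387.6 − 365×0.39/0.61 = 154
- TVR: 1,396.5 − 365×0.77/0.23 = 175
- Difference: about 20 days

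Restricted mean days without a job, over 365 days, all randomised = p/λ:
- SE: 0.61 × 387.6 = 236
- TVR: 0.23 × 1,396.5 = 321
- Difference: about 85 days

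The finders-only comparison shows about a quarter of the difference in time without work.

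**4. Simulation, 62 per arm, 5,000 trials per pattern.** All patterns reach 61% and 23% by 12 months. The capped t-test gives non-finders the full 12 months.

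| Assumed timing of job starts | Finders' mean, SE minus TVR | Finders-only t-test significant for SE | Finders-only t-test significant for TVR | Log-rank significant for SE | Capped t-test significant for SE |
|---|---|---|---|---|---|
| Constant hazard | −20 days | 9–10% | 0.3% | 99% | 98% |
| SE finders even over months 0–12, TVR finders even over months 0–6 | +92 days | 0% | 91% | 97% | 61% |
| 20% of each arm in months 0–3, then a further 41% (SE) or 3% (TVR) over months 3–12 | +99 days | 0% | 89% | 97% | 60% |

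Under constant hazard, the finders-only estimate has the wrong sign in 27–28% of trials.

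**5. The reversal by hand.** Suppose both arms place the same 23% at mean day 60, and SE places a further 38% evenly over months 4–12 (mean day 242.5).
- Finders' means: SE (23×60 + 38×242.5)/61 = 174; TVR 60. SE looks 114 days slower.
- Restricted means, all randomised: SE 0.23×60 + 0.38×242.5 + 0.39×365 = 248; TVR 0.23×60 + 0.77×365 = 295. SE is 47 days better.

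In this example SE is at no time behind TVR in the share employed, yet the finders-only comparison favours TVR.

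**The case against.** The strongest reply is that the article does not commit to the faulty analysis. The list of methods is introduced by a word that leaves it open, and log-rank and Cox are standard methods too. No sentence assigns a t-test to days to employment or limits that analysis to job finders. The intention-to-treat sentence points away from such a limit. A condensed article may also leave the test for each supplementary indicator to an analysis plan that is not shown. All of this stands as a limit on the claim: a reader might infer that a finders-only t-test is prescribed, and the text does not say that. What remains is more than a missing detail. The article does state a rule for continuous outcomes, it lists a continuous outcome that the rule does not fit, and intention to treat cannot be followed for that outcome without a further rule for people who have no value.

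Second, a t-test need not drop anyone. With non-finders set to 365 days it keeps about 98% power under constant hazard, close to the log-rank test. That is correct, so the low power in the first row of the table comes from excluding non-finders and not from the t-test as such. But the article gives no capping rule, and the capped test falls to about 60% under the early-finder patterns, where log-rank keeps about 97%.

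Third, a reader might extend the point to amount and duration of work and to wages. The documents do not support that. Zero is a natural value for someone who did not work, and nothing says these measures will be computed among workers only.

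**Conclusion.** The point holds at moderate severity. The article lists a right-censored outcome, and the only method it states for continuous data cannot use censored values without a rule that the article does not give. Applied to the observed values, the t-test would rest on about 52 of 124 participants, in unequal fractions of the two arms, against the article's own intention-to-treat statement.

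The size depends on two assumptions: that 61% and 23% are 12-month rates, and the timing of job starts. Under constant hazard the comparison mostly misses the effect (about 20 days shown against about 85; power about 10% against 99%), but its expected direction still favours SE. A significant reversal appears only under the early-finder patterns. Those were constructed to show that it can happen, and nothing in the article says that TVR finders will be early. It would be wrong to read this as a prediction that SE will look slower.

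Nor is the trial's main result in danger. The primary outcome is binary, suits the chi-square test named for it, and carries the sample size. The exposure is confined to one additional indicator.

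**What to change.** State in the Statistical analyses section, or in the analysis plan before outcome data are seen, that time to first competitive employment will be analysed in all randomised participants, with those not employed by day 365 censored at that day. Present Kaplan-Meier curves by arm, compare arms by a log-rank test or Cox model, and report the difference in restricted mean time to 12 months with its confidence interval. The restricted mean is a useful effect measure here because it is in days and does not rely on proportional hazards.

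If a mean number of days among job finders is also reported, label it as descriptive and not as a comparison of randomised groups.

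The cost is a few sentences. The indicator already requires the date of the first job, so no new data are needed, and the sample size and primary analysis stay as they are.
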